## Abstract

**Background:**

Disorders of consciousness (DoC) are severe neurological conditions in which consciousness is impaired to various degrees. They are caused by injury or malfunction of neural systems regulating arousal and awareness. Over the last decades, major efforts in improving and individualizing diagnostic and prognostic accuracy for patients affected by DoC have been made, mainly focusing on introducing multimodal assessments to complement behavioral examination. The present EU-funded multicentric research project “PerBrain” is aimed at developing an individualized diagnostic hierarchical pathway guided by both behavior and multimodal neurodiagnostics for DoC patients.

**Methods:**

In this project, each enrolled patient undergoes repetitive behavioral, clinical, and neurodiagnostic assessments according to a patient-tailored multi-layer workflow. Multimodal diagnostic acquisitions using state-of-the-art techniques at different stages of the patients’ clinical evolution are performed. The techniques applied comprise well-established behavioral scales, innovative neurophysiological techniques (such as quantitative electroencephalography and transcranial magnetic stimulation combined with electroencephalography), structural and resting-state functional magnetic resonance imaging, and measurements of physiological activity (i.e. nasal airflow respiration). In addition, the well-being and treatment decision attitudes of patients’ informal caregivers (primarily family members) are investigated. Patient and caregiver assessments are performed at multiple time points within one year after acquired brain injury, starting at the acute disease phase.

**Discussion:**

Accurate classification and outcome prediction of DoC are of crucial importance for affected patients as well as their caregivers, as individual rehabilitation strategies and treatment decisions are critically dependent on the latter. The PerBrain project aims at optimizing individual DoC diagnosis and accuracy of outcome prediction by integrating data from the suggested multimodal examination methods into a personalized hierarchical diagnosis and prognosis procedure. Using the parallel tracking of both patients’ neurological status and their caregivers’ mental situation, well-being, and treatment decision attitudes from the acute to the chronic phase of the disease and across different countries, this project aims at significantly contributing to the current clinical routine of DoC patients and their family members.

**Trial registration:**

ClinicalTrials.gov, NCT04798456. Registered 15 March 2021 – Retrospectively registered.

## Background and objectives

### Background

Severe brain injuries following traumatic or non-traumatic etiologies can lead to Disorders of Consciousness (DoC), a class of neurological conditions characterized by pathological alterations of arousal and/or awareness. DoC patients are highly heterogeneous regarding type, extent, and location of the underlying structural and functional brain pathology as well as in terms of their clinical phenotype [1]. The DoC range from coma (patients’ eyes closed) to unresponsive wakefulness syndrome (UWS; eyes open either passively or in response to stimulation) - also known as vegetative state (VS) - to minimally conscious state (MCS; divided into “MCS-“: visual pursuit oberservable without signs of command following, and “MCS+”: command following without effective communication) [2, 3].

The diagnostic and prognostic tests available for DoC in the current clinical practice demonstrate an unacceptably high misdiagnosis rate of approximately 40% [4]. Although diagnostic accuracy can be improved by the application of well-established standardized behavioral rating scales such as the Coma Recovery Scale-Revised (CRS-R) [5], these scales still lack optimal sensitivity (as they require the preservation of patient’s sensory, motor and executive functions) [6, 7], and specificity (due to the lack of a ground-truth about consciousness in many patients with DoC) [8]. Hence, behavioural assessments may fail to detect consciousness in DoC patients due to injury-induced individual cognitive, sensory or motor deficits. Meta-analyses suggest that up to 15–20% of DoC patients are likely to exhibit covert signs of consciousness or cognitive-motor dissociation (CMD) [9], while seeming unresponsive purely based on behavioral bedside examinations [10, 11].

Current guidelines on the diagnosis of DoC recommend multimodal evaluations using a combination of standardized neurological examinations, (functional) neuroimaging, and neurophysiological tools in order to improve and individualize diagnostic and prognostic accuracy [12]. In particular, using innovative functional neurodiagnostic methods, which do not require behavioral command following of the examined patient, covert markers of consciousness can be detected and, in turn, diagnostic accuracy can be increased [13, 14]. Among these recommended methods, quantitative electroencephalography (qEEG), functional magnetic resonance imaging (fMRI), and EEG combined with transcranial magnetic stimulation (TMS-EEG) have shown promising results [10, 12, 15, 16]. Combining evidence obtained from different neurodiagnostic multimodal techniques and analyzing them with modern machine learning-based methods can further increase diagnostic accuracy [14, 17].

However, despite major progress in accurate diagnosis and outcome prediction for DoC patients over the last years [10], as to date, reliable prognostic indices and read-outs to prognosticate a patient’s clinical evolution are still missing [18]. Moreover, the etiology and pathophysiology of DoC are highly heterogeneous [19], and most likely result from the combination of several factors, whose role and interplay still need to be clarified. Similarly, the precise neuronal mechanisms underpinning consciousness and its loss and recovery are still poorly understood, especially at the individual patient level. However, for ethical, therapeutic, and economic reasons, it is imperative to improve diagnostic accuracy and to predict outcome as early, reliably, and accurately as possible [20–22]. Indeed, many medical decisions and further treatment or rehabilitation paths crucially rely on accurate diagnostic and prognostic results [23, 24].

In addition, more reliable diagnosis and prognosis are of utmost relevance not only for patients’ management but also for the patients’ family members who very often become their informal caregivers. Taking care of DoC patients is a highly stressful experience for relatives and can represent a great emotional burden for them. Informal caregivers are exposed to substantial life changes and consequently often report low mental and physical health as well as high levels of distress [25]. These burdens are related to the ambiguity of the situation they are facing, and especially to the uncertainty of its duration and outcome [26, 27]. At the same time, they might need to act as surrogate decision-makers for their loved ones. Neuroimaging evidence of covert consciousness could confront them with ethical challenges [28]. For these reasons, the development of personalized tools to improve diagnosis and prognosis of DoC as well as their comprehensive communication are of utter importance for both patients and their family members.

### Aims

The overall goal of the multicenter European PerBrain project (full project title: “PerBrain: A Multimodal Approach to Personalized Tracking of Evolving State-Of-Consciousness in Brain-Injured Patients”) is to optimize the diagnosis and long-term prognosis of DoC patients following acute brain injury by combining clinical and multimodal tools. The project aims at developing a hierarchical diagnosis and prognosis procedure that allows a personalized description of the neurological status and the expected recovery potential at the single patient level.

The hierarchically applied methods include a wide range of the state-of-the-art neuroimaging-based (structural MRI and fMRI) and neurophysiological-based (qEEG and TMS-EEG) techniques as well as the investigation of brain-body interactions (recordings of nasal respiration during rest and during odor presentation). Further, well-established standardized clinical behavioral scales for the assessment of consciousness are administered (CRS-R, Glasgow Outcome Scale Extended GOS-E). Data from the different investigation modalities will then integrated by employing newly developed biostatistical analysis based on machine learning with the aid of information technology. In this way, a better understanding of the pathophysiological mechanisms of DoC is expected to be gained, consequentially enabling more tailored rehabilitation strategies and improving prognosis at single patient level.

In parallel to the optimal definition of the patients’ neurological status, PerBrain aims at investigating factors that impact well-being of informal caregivers of DoC patients and their treatment decision attitudes, specifically when confronted with results of multimodal technology-based tests, with the goal to develop strategies for the effective communication of technology-based results specifically tailored to caregivers’ needs.

## Methods

### Study design and data collection

PerBrain is an international, multicentric, longitudinal mixed-methods project focusing on tracking the neurological status of DoC patients and the needs of their informal caregivers over the period of one year. It is coordinated by the Institut du Cerveau, Paris, and includes the following project partners: Department of Biomedical and Clinical Science of the University of Milano, Italy, IRCCS Santa Maria Nascente Fondazione Don Carlo Gnocchi ONLUS, Italy, Weizmann Institute of Science, Israel, University Hospital of the Ludwig-Maximilians-Universität München, Germany, and Therapiezentrum Burgau Hospital for Neurorehabilitation, Germany.

Each patient undergoes at least five standardized clinical examinations with the CRS-R within two weeks to establish a stable clinical diagnosis of consciousness before the first multimodal assessment takes place. Subsequently, in order to track the patient’s clinical evolution, neurophysiological assessments are performed at three time points within one year after injury: in the acute phase (T0; 1 - 2 months after injury), subacute phase (T1; 4 - 7 months after injury) and chronic phase (T3; 9 - 12 months after injury). The clinical and multimodal assessment includes 1. multiple behavioral evaluations using gold-standard scales (GOS-E and CRS-R), 2. neurophysiological evaluations based on qEEG (resting-state and task-based paradigms), and, where available, TMS-EEG, 3. neuroimaging evaluations based on structural MRI and resting-state fMRI, and 4. finally also repeated nasal airflow and respiration measurements (24 h rest recording and odor dependent). For a compilation of the study visits, see Table 1.

**Table 1 Tab1:** Overview of patient (T1, T2, T3) and caregiver (C0, C1, C2, C3) assessments

C0 Before patients’ assessment	T1 1-2 m from injury	C1 1-2w after results communi-cation	T2 4-7 m from injury	C2 1-2w after results communi-cation	T3 9-12 m from injury	C3 1-2w after results communi-cation
Personal data FCV-19S Religious/ spiritual information BIPQ EQ-5D-5L AcQoL HADS RS14 SOC-13 Treatment choices survey	Patient’s multimodal assessment ^a^ + Doctor’s communication of results to caregivers	FCV-19S BIPQ EQ-5D-5L HADS + qualitative interview (N = 9)	Patient’s multimodal assessment ^a^ + Doctor’s communication of results to caregivers	FCV-19S BIPQ EQ-5D-5L AcQoL HADS Treatment choices survey	Patient’s assessment at home (CRS-R & GOS-E)	FCV-19S Religious/ spiritual information BIPQ EQ-5D-5L AcQoL HADS RS14 SOC-13

*m* months, *w* weeks, *FCV-19S* Fear of COVID-19 Scale; *BIPQ* Brief Illness Perception Questionnaire, *EQ-5D-5L* European Quality of Life-5 Dimensions, *AcQoL* Adult Carer Quality of Life Questionnaire, *HADS* Hospital Anxiety and Depression Scale, *RS14* 14-Item Resilience Scale, *SOC-13* 13-item Sense of Coherence Scale

^a^ Patient’s multimodal assessments at T1 and T2 include behavioral scales (CRS-R, GOS-E), qEEG, TMS-EEG, structural and functional MRI, and nasal respiration measurements (24h and odor dependent).

In case the patient’s legal surrogate gave informed written consent for the patient to take part in the research (patient study part), the patients’ family caregivers are asked to participate in the caregiver study part as well. For participating caregivers, quantitative and, for a subset of them, qualitative data concerning their psychological well-being, informational needs about their relative’s condition, and expectations are collected. For each included caregiver, four assessments are set (time points C0, C1, C2, and C3), comprising different subsets of questionnaires (see Table 2) which are in relation to the patients’ assessments (c.f. Table 1).

**Table 2 Tab2:** Collected quantitative and qualitative caregiver data

Data	C0	C1	C2	C3
Sociodemographic characteristics	x			
Religious/spiritual information	x			x
FCV-19S	x	x	x	x
BIPQ (adapted to caregivers)	x	x	x	x
EQ-5D-5L	x	x	x	x
ACQoL	x		x	x
HADS	x	x	x	x
RS14	x			x
SOC-13	x			x
Treatment choices survey	x		x	
Qualitative interview		x		

Timepoints: C0 (before diagnostics), C1 (after T1, 1-2 months after onset of DoC), C2 (after T2, 4-7 months after onset of DoC), C3 (after T3, 9-12 months after onset of DoC)

Pseudonymised data from patients and caregivers as well as patients‘ metadata associated to their neuroimaging and physiological evaluations are collected and managed using a custom longitudinal REDCap data base [29, 30]. The database was structured in events (enrollment, clinical evaluation, EEG evaluation, nasal respiration measurements, TMS-EEG, MRI, caregiver appointments C0, C1, C2 and C3) and for each event specific forms were constructed to store relevant information of patients and their corresponding caregivers. The enrollment event contains forms related to demographics, injury etiology, patients’ medical history and transfers. In the clinical evaluation event, the CRS-R and GOS-E examinations item scores are collected. For the EEG evaluation event, the metadata associated to the recording settings for the resting-state, and task-based protocols (local-global and motor command protocol) are stored. The brain-body interactions event contains forms to collect metadata regarding the odor response and the 24hs respiration recordings. For the TMS-EEG event, the metadata associated with this procedure is stored. In the MRI event, forms to collect metadata related to fMRI during resting state and structural MRI were implemented. Information regarding the medication administered to the patient at the moment of each evaluation is also listed. As for the caregivers' events (C0, C1, C2, and C3) the items response for the above described subsets of questionnaires were stored. This longitudinal database, hosted at Paris Brain Insititute, unifies and centralizes the information collected by all partners ensuring data consistency and accessibility across centers.

### Participant recruitment and sample size

Two main groups of participants are enrolled for the PerBrain project: brain-injured DoC patients and their informal caregivers. Patients’ screening takes place at the Pitié-Salpêtrière Hospital, Paris (France), IRCCS Santa Maria Nascente Fondazione Don Carlo Gnocchi ONLUS, Milan (Italy), Loewenstein Hospital Rehabilitation Center, Raanana (Israel), University Hospital of the Ludwig-Maximilians-University, Munich (Germany), and Therapiezentrum Burgau Hospital for Neurorehabilitation, Burgau (Germany). Study inclusion takes place after the informed written consent of the patient’s legal guardian / next-of-kin has been obtained. After inclusion of a patient into the study, a patient’s relatives are invited to participate in the research as well. Participant recruitment started in September 2020 and data collection will last until at least April 2023. In total, 150 patients and 80 informal caregivers are expected to be enrolled.

### Eligibility criteria

#### 
DoC patients

DoC patients between 18 and 85 years are screened for study participation. Informed written consent must be provided by the patient’s legal guardian or, in case no legal guardian has been assigned yet, by the closest relative. As soon as a legal guardian has been appointed, he/she is asked to renew consent.

Exclusion criteria comprise pre-existing DoC, continuous medical sedation (induced coma), use of barbiturates for sedation, clinical instability, severe motor agitation, marked difficulty maintaining vigilance throughout the procedure, terminal malignant disease (as it increases the likelihood of not being alive for the 12-month follow-up assessment T3), prediction of highly unlikely survival until the time of the 12-month follow-up due to conditions such as multi-organ failure based on the judgment of the critical care physician, palliative care setting, withdrawal of life-support, and pregnancy.

For MRI and TMS-EEG assessments, the present study complies to specific contraindications (magnetic material in or on person such as pacemakers, defibrillators, intracranial metal implant, metal prostheses not compatible with MRI investigations). Formerly included DoC patients drop out of the study in case of palliative care setting or death.

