Following rejection of trials containing noise or muscle artifacts, EEG data are average referenced, high-pass filtered (1 Hz) and baseline corrected over 400 ms pre-stimulus. Independent Component Analysis (ICA) is applied to reduce ocular and residual muscle artifacts. Finally, data are low-pass filtered at 45 Hz. For each cortical target, a TMS-evoked response is obtained by averaging 150-250 artifact-free single trials. In order to obtain the overall amount of electrical activity induced by TMS, the Global Mean Field Power (GMFP) is computed from the multichannel average. Source modeling of TMS evoked potentials is performed only at the latencies corresponding to significant GMFP activations. To assess the threshold for significance, a bootstrap method (which does not assume normality) is applied by shuffling the time samples of pre-stimulus activity (from -300 to -50 ms) at the single-trial level and by calculating 500 surrogated pre-stimulus GMFPs. From each random realization, the maximum value across all latencies is selected to obtain a maximum distribution (control for type I error) and significance level is set at p<0.01. A similar procedure is applied to TMS-evoked responses recorded at single EEG channels. To evaluate the occurrence of pathological OFF-periods that may disrupt the emergence of global complex cortico-cortical interactions, time-frequency decomposition of TEPs is computed as described in [40]. Following theoretical considerations that link consciousness to the observation of complex EEG activity patterns that are integrated and differentiated at the same time, the Perturbational Complexity Index (PCI) [37, 43] is computed for each stimulation site and the individual maximum PCI value is used for diagnostic purposes. The prognostic contribution of all these neurophysiological measures is evaluated by comparing their longitudinal modulation with the clinical evolution of the patient. Notably, the tools and procedures described above will be shared by the Italian unit, which in the last two decades significantly contributed to the TMS-EEG field, with the German unit, the only other one provided with the proper equipment to carry out TMS-EEG measurements.

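### Death and entry to palliative care end a patient's participation in a prognosis study, so follow-up is lost at events that carry prognostic information

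*Protocol article*

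**What the plan says.** Visit labels here follow Table 1 of the protocol article (T1, T2, T3).

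- **Goal.** Under Aims, the project is meant to "optimize the diagnosis and long-term prognosis of DoC patients following acute brain injury".
- **Drop-out rule.** Under Eligibility criteria, DoC patients: "Formerly included DoC patients drop out of the study in case of palliative care setting or death". The sentence has no qualification.
- **Entry criteria.** The same section excludes patients already in palliative care, patients with life-support withdrawn, and those judged very unlikely to survive to the 12-month assessment. One exclusion is justified by the risk of losing the final visit: "terminal malignant disease (as it increases the likelihood of not being alive for the 12-month follow-up assessment T3".
- **Final outcome.** In Table 1, T3 (9-12 months) is "Patient’s assessment at home (CRS-R & GOS-E".
- **Disclosure.** Table 1 also places the doctor's "communication of results to caregivers" at T1 and T2.
- **Prognostic analysis.** Under TMS-EEG: "The prognostic contribution of all these neurophysiological measures is evaluated by comparing their longitudinal modulation with the clinical evolution of the patient".
- **Database.** Under Study design and data collection: "In the clinical evaluation event, the CRS-R and GOS-E examinations item scores are collected". The events listed there do not include one for death, vital status or withdrawal.

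The article does not describe the analysis set for prognosis or how missing T3 outcomes are handled.

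**The concern.** In a one-year prognosis study after brain injury, death is one of the results to be predicted. The rule treats it as attrition, together with entry to palliative care. T3 is an examination that only living patients still in the study can have, so neither group contributes a T3 outcome.

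The loss is not random. Death says directly how the patient fared. A move to palliative care reflects how the patient was judged to be faring, and that judgement may draw on the markers under study, because results are disclosed after T1 and T2. The Discussion itself says that diagnosis bears on decisions about life-sustaining therapy, and that underestimating consciousness can lead to care being withdrawn. Drop-out can therefore depend on both the marker and the prognosis.

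At stake is the population to which the prognostic results apply. A clinician making a prediction at T1 does not know who will survive and stay in the study, so estimates conditional on that group do not answer the question asked at T1.

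**Working it through.** The plan gives no figure to reproduce. It states an expected enrolment of 150 patients, but no death, palliative-care, drop-out or recovery rate. All rates below are assumptions.

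**1. Recovery share if only completers are analysed.** Let d be the share dropped and r the recovery share among all enrolled, with no dropped patient recovering. Completer recovery = r/(1-d), so the inflation factor is 1/(1-d).

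| d | Dropped of 150 | Factor | r = 20% reads as | r = 40% reads as |
|---|---|---|---|---|
| 5% | 7.5 | 1.05 | 21.1% | 42.1% |
| 10% | 15 | 1.11 | 22.2% | 44.4% |
| 20% | 30 | 1.25 | 25.0% | 50.0% |
| 30% | 45 | 1.43 | 28.6% | 57.1% |
| 40% | 60 | 1.67 | 33.3% | 66.7% |

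If all 150 stay in the denominator with death counted as an outcome, this overstatement is zero.

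**2. Palliative transitions.** No recovery is certain for deaths. For palliative transitions, let q be the share who would have recovered under continued care. All-enrolled recovery = (completer recovery)(1-d) + q·d. With d = 20% and completer recovery 25%:

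- q = 0: 0.25 × 0.80 + 0 = 20%, so completers overstate by 5 points.
- q = 25%: 0.20 + 0.05 = 25%, no difference.
- q = 50%: 0.20 + 0.10 = 30%, so completers understate by 5 points.

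**3. Marker accuracy, as a table.** Assume 150 patients, 30% favourable (45), sensitivity and specificity both 0.80. Then TP = 36, FN = 9, TN = 84, FP = 21. Drop 30 patients, all unfavourable, and vary how many are marker-negative:

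| Marker-negative among dropped | TN, FP left | Specificity | Favourable among marker-negatives |
|---|---|---|---|
| none dropped | 84, 21 | 84/105 = 0.80 | 9/93 = 9.7% |
| 90% (27 of 30) | 57, 18 | 57/75 = 0.76 | 9/66 = 13.6% |
| 80% (24 of 30) | 60, 15 | 60/75 = 0.80 | 9/69 = 13.0% |
| 50% (15 of 30) | 69, 6 | 69/75 = 0.92 | 9/78 = 11.5% |

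Specificity falls, stays or rises according to who is dropped. Favourable outcome among marker-negatives rises in all three cases, but only because every dropped patient is assumed unfavourable.

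**4. Marker accuracy, as AUC.** A normal marker with SD 1 was simulated, with mean 0.5 in recovered and -0.5 in non-recovered patients, and recovered, non-recovered and dropped patients in the ratio 3:4:2. Completer AUC is 0.76. With the dropped patients counted as non-recovered, AUC is 0.79, 0.76, 0.72 or 0.67 when their marker mean is -1.0, -0.5, 0 or 0.5. The direction is again open.

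**The case against.** The strongest reply is that dropping out of the study is not the same as being left out of the analysis. The article nowhere says that T1 or T2 data are discarded, that deaths go unrecorded, or that prognosis is analysed in completers only. A patient who has died cannot attend T3, so the rule may mean no more than the end of assessments. Analysis sets are commonly left to a full protocol or SAP, neither of which is shown, and the list of database events is condensed. All of this stands. A reader might infer that the worst outcomes are deleted from the prognosis data and that recovery and marker accuracy are therefore biased in a known direction. The document does not support that: the completer-only step is an inference, and steps 2 to 4 show that the direction is settled only for deaths.

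It also stands that counting every death after a palliative transition as an ordinary unfavourable outcome has a cost of its own. If a disclosed marker helped bring about the decision, the marker would be credited with an outcome it had influenced.

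Two further points narrow the concern. The entry criteria already select for expected survival, and the section on multilayer integration describes the added diagnostic value of combining modalities as a critical aim. Diagnostic classification at T1 or T2 does not need T3.

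What does not stand is leaving the matter to an SAP. An analysis plan can classify deaths that are known. It cannot supply outcomes for patients whose follow-up ended when they entered palliative care. That is a data-collection rule, and it is fixed in this document.

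**Conclusion.** The rule conflicts with the prognostic aim and should be changed. Death and palliative transition are both informative about prognosis, and the latter may be influenced by the disclosed results. With follow-up ending at either event, prognostic estimates would apply to survivors who remain in the study, a group not identifiable at T1.

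The size cannot be stated, because the article gives no rates. Under a completer-only analysis in which no dropped patient recovers, recovery is overstated by 1/(1-d), for example 25% read in place of a true 20% when an assumed 20% are dropped. That direction is certain for deaths and open for palliative transitions. The effect on specificity and AUC can go either way. The point is a should-fix: the prognostic part is exposed, while same-visit diagnostic analyses at T1 and T2 are not affected by later drop-out.

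**What to change.** Amend the drop-out sentence so that study acquisitions stop at these events but the patient stays in the outcome dataset. Specifically:

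- Record vital status, date and reason for every enrolled patient.
- After a palliative transition, obtain GOS-E from the chart or by telephone where consent allows.
- Count death as an outcome in the prognostic analysis.
- Handle palliative transition or withdrawal of life-support as a separate (competing or intercurrent) event. Add sensitivity analyses that count the deaths following it as unfavourable and that set those deaths apart.

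This concerns data collection and analysis only and touches no clinical decision. The cost is a short amendment, any vital-status and reason fields the database lacks, and a small chart or telephone burden without a new visit. Reported recovery rates are likely to look less favourable. For patients already dropped under the present rule, the same information could be sought retrospectively from charts or by telephone where consent allows.
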